#### Secondary outcomes

The secondary outcomes are as follows:Patients’ satisfaction with the patient-physician interaction is measured using the ZUF-8 [13] (German version of the Client Satisfaction Questionnaire, CSQ-8 [14]). We expect a 1-point mean increase (scale 8–32) between the intervention group and the control group after patients have been treated (at the end of the ED visit before discharge, in exceptional cases by telephone within 72h). In contrast to the PSQ, the CSQ measures satisfaction with the provided health care services.Anxiety is measured using a visual analog scale (VAS-A) [15] at baseline, after the symptom assessment, and at the end of the ED visit. We expect that the potential increase in anxiety after symptom assessment from the baseline value will not be higher than 5 points in the intervention group and that the proportion of patients leaving the ED with higher anxiety values than at baseline will not be higher in the intervention group than in the control group.Physicians’ satisfaction with the patient-physician-interaction as measured by the mean score of the physician version of the Patient Satisfaction Questionnaire (PSQ, physician version) [12]. The intervention regarding this endpoint is considered successful if we find a mean difference in means of at least 5 points (scale 0–100) in the intervention group compared to the control group after patients have been treated.

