#### Secondary objectives

To investigate the impact of a SAA prior to the first physician encounter among self-referred walk-in patients in the ED setting on satisfaction with the received care at the end of the ED visit.To investigate the impact of a SAA prior to the first physician encounter among self-referred walk-in patients in the ED setting on anxiety of participants.To investigate the impact of a SAA prior to the first physician encounter among self-referred walk-in patients in the ED setting on physicians’ satisfaction with the patient-physician interaction after the patient-physician encounter.

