### Trial design {8}

The study is a parallel-group, multi-center superiority trial with a randomization allocation ratio of 1:1 to either using a SAA before the physician encounter or physician encounter only (standard care) among non-urgent, self-referred walk-in patients in the ED.

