## Interventions

### Explanation for the choice of comparators {6b}

Patients in the control group proceed as usual and only complete questionnaires at the beginning of their waiting period and at the end of the ED visit. Otherwise, they wait without further intervention and receive standard care to ensure that the experimental intervention can be compared to the regular ED procedure. In extraordinary circumstances, patients can be contacted via telephone for up to 72 h to reduce loss-to-follow-up.

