## Statistical methods

### Statistical methods for primary and secondary outcomes {20a}

R 4.0.2 or higher (R Core Team, 2022) and SAS 9.4 (SAS Institute, USA) will be used to perform statistical analyses. Baseline characteristics will be presented as percentages (binary data), median and interquartile range (ordinal data), and mean and standard deviation (continuous data). The primary efficacy endpoint is the mean difference in the patients’ rating of patient-physician interaction (PSQ-5) between the intervention group and the control group after patients have been treated (final value) and will be analyzed with a linear mixed model accounting for recruiting site. Secondary and exploratory efficacy endpoints will be analyzed using (generalized and mixed) linear models. Reporting will include the estimator, 95% confidence intervals, and respective *p* values. No adjustments of *p* values due to multiplicity are planned.

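### Anxiety is judged by an uncontrolled rise in the app arm and an any-increase proportion without a margin; the end-of-visit score, available in both arms, would be the better basis

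*Protocol article*

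**What the plan says.** The objective is neutral: to study the impact of the app "on anxiety of participants" (Protocol article, Secondary objectives). Under Secondary outcomes, anxiety is measured by VAS-A "at baseline, after the symptom assessment, and at the end of the ED visit", and two expectations follow:

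- **Expectation A**, in one arm: "potential increase in anxiety after symptom assessment from the baseline value will not be higher than 5 points in the intervention group".
- **Expectation B**, between arms, compared with controls: "the proportion of patients leaving the ED with higher anxiety values than at baseline will not be higher in the intervention group". No margin is given.

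The comparator section {6b} says that controls "only complete questionnaires at the beginning of their waiting period and at the end of the ED visit". Trial design {8} describes a "multi-center superiority trial with a randomization allocation ratio of 1:1". On analysis, section {20a} says: "Secondary and exploratory efficacy endpoints will be analyzed using (generalized and mixed) linear models". It adds that estimates, 95% confidence intervals and p values will be reported.

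**The concern.** Both expectations say that the app is no worse, and each is tied to a quantity that answers this poorly.

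Expectation A is a before-after change in one arm. Anxiety may drift while a patient waits, whether or not an app is used, and without a control value at that time the drift cannot be separated from the app. The error can go either way: a real rise caused by the app can be hidden, or a waiting-room rise can be blamed on it.

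Expectation B is randomised, but it counts a trivial rise and a large one alike. Without a margin, nothing says how large an excess the data must exclude before the arms can be called no different.

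Anxiety is the one outcome for which the protocol itself names a potential increase after the intervention. Other harm capture is a free-text field and contact persons (section {22}). A wrong statement on anxiety would bear on the use of the app in acute care, which the Discussion gives as the purpose of the trial.

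**Working it through.** **1. The plan's own sample size.** Inputs from section {14}: standardised difference 0.3, two-sided α 0.05, power 0.80, drop-out 20%. The exact t-test solution is 175.4, so 176 per arm and 352 in total; 352 / 0.8 = 440. The stated figures reproduce. They concern the PSQ; no calculation is given for anxiety. I use 176 evaluable per arm below.

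**2. Which anxiety values exist in which arm** (Secondary outcomes and section {6b}):

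| Time | App arm | Control arm |
|---|---|---|
| Baseline | yes | yes |
| After symptom assessment | yes | no |
| End of visit | yes | yes |

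Table 1 marks secondary outcomes after symptom assessment without separating the arms, but section {6b} limits controls to the first and last times.

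**3. Expectation A.** Observed change = drift while waiting + effect of the app. As an illustration, take a drift of −4 points and an app effect of +8. The observed change is −4 + 8 = +4, which satisfies the 5-point limit although the app raised anxiety by 8. The planned confidence interval does bound the change: its half-width is 1.96 × SD / √176, or 2.2 points at an assumed SD of change of 15 and 5.9 at 40. It bounds change over time, not the effect of the app.

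**4. Expectation B.** The document gives no proportions, so these are assumed.

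- *Precision* at 30% in both arms: 1.96 × √(2 × 0.3 × 0.7 / 176) = 9.6 percentage points. For 10% to 40% the half-width runs from 6.3 to 10.2.
- *Power against 30% versus 40%*: SE = √((0.21 + 0.24) / 176) = 0.0506; Φ(0.10 / 0.0506 − 1.96) = Φ(0.02) = 0.51 (0.50 with the pooled variance under the null).
- *Power against a 10-point worsening* (pooled-null formula) for control proportions of 10 / 20 / 30 / 40%: 75 / 58 / 50 / 47%.
- *Implied margin of zero*: if the arms are truly equal, the upper 95% limit lies below zero in only 2.5% of trials. Read by the point estimate alone, the app arm comes out higher about half of the time.

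**5. The alternative: end-of-visit VAS-A adjusted for baseline.** The SD and the baseline-to-end correlation r are assumptions, and 5 points is used as a candidate margin.

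SE = SD × √(1 − r²) × √(2/176); power to exclude the margin when the true difference is zero = Φ(5/SE − 1.96). With r = 0.6, √(1 − r²) = 0.8.

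| SD | SE, adjusted | Power, adjusted | Power, change score |
|---|---|---|---|
| 20 | 1.71 | 83% | 75% |
| 25 | 2.13 | 65% | 56% |
| 30 | 2.56 | 50% | – |

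The change-score column replaces SD × √(1 − r²) by SD × √(2(1 − r)). Adjustment gains 8 to 9 points of power, but power is modest once the SD reaches 25.

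**The case against.** A reader might infer that the trial cannot show that the app does not raise anxiety. The documents do not support that. VAS-A is collected in both randomised arms at baseline and at the end of the visit, and section {20a} commits to 95% confidence intervals, so an increase at the end of the visit can be bounded. A linear model is also a proper vehicle for a no-worse reading.

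A reader might also infer that the investigators will take p > 0.05 as proof of no increase, or that these are confirmatory safety claims. Neither is stated. The anxiety text speaks of what is expected, the objective is neutral, and the success wording used for the PSQ endpoints is not used here. Decision rules and margins may stand in a fuller protocol or analysis plan that is not shown.

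Some supporting arguments also fall away. The document gives no range for the VAS-A. Eligibility does not select on anxiety, so regression to the mean is not established; drift while waiting is enough for the argument. The 5 points was set for a within-arm change and is not already a between-arm margin. Expectation B could be demonstrated if the app lowered anxiety.

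Two things remain. No later document can supply the missing control value after symptom assessment. And the one randomised anxiety comparison that the article names is the dichotomy, although the continuous end-of-visit score is available in both arms.

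**Conclusion.** The point holds in a limited form. Expectation A cannot be attributed to the app; this follows from the measurement times and needs no assumption. Expectation B is an inefficient comparison without a margin. At 176 per arm, a true 10-point worsening would be missed in about 25% to 53% of trials over assumed control proportions of 10% to 40%, so non-significance would not support it. These proportions, and the SD and correlation of the VAS-A, are not in the document. The point concerns one secondary outcome and leaves the primary analysis untouched. It is a worthwhile improvement, using a better method on data already planned, and not a defect that stops the trial from informing on anxiety.

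**What to change.** - Make the main anxiety analysis the between-arm difference (app minus control) in end-of-visit VAS-A, in a linear model adjusted for baseline VAS-A and site.
- Allow a statement of no relevant increase only if the upper 95% confidence limit lies below a margin stated and justified in advance. The protocol's 5 points is a candidate, but its use between arms needs its own reasoning.
- Report the change after the app, and the risk difference for any increase, descriptively with 95% confidence intervals and without causal wording.

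Cost: wording only, as all the data are already planned. A reassuring conclusion becomes harder to reach and may be underpowered (about 83% at SD 20 and 65% at SD 25, with r 0.6 and a 5-point margin; lower for larger SDs). The end-of-visit score is taken after the physician encounter, so the app's immediate effect on anxiety stays uncontrolled; only a control VAS-A at a matched waiting time would change that.

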#### Other outcomes

Further, we want to assess additional outcomes relating to the SAA. Most of these outcomes are measured in patients of the intervention group exclusively:Certainty in participants’ self-triage decision is measured with a visual analog scale. We consider a 5-point mean difference from baseline to after symptom assessment to be a relevant difference in the intervention group.Trust in the symptom checker is measured using a two-item Likert scale.Trust in the physician is measured using the trust scale of the Cologne Patient Questionnaire (CPQ) [16] in both groups.Usability and usefulness is measured using the System Usability Scale (SUS) [17], the mHealth App Usability Questionnaire (MAUQ) [18], and a self-developed questionnaire for the intervention group only.Diagnostic accuracy is measured by comparing the recommendations of the SAA with diagnoses given in the ED, after discharge and by an independent, external, expert panel blinded to the recommendation given by the app.Triage accuracy is measured by comparing the recommendation of the SAA with the MTS, triage appraisal of the treating physician in the ED, and by an independent, external, expert panel blinded to the recommendation given by the app for cases where discrepancies occurred.

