### Intervention description {11a}

Eligible patients randomized to the intervention group will use the SAA Ada (© 2021 Ada Health GmbH: www.ada.com). Patients will be asked to use Ada once to assess their symptoms on a study tablet—which will be provided by the study nurses—while waiting in the ED before their first consultation with a physician. Once completed, they receive a list of possible diagnoses and an estimation of their complaints’ urgency from the SAA. The assessment and recommendations are printed by the study personnel and will be provided to the treating physician before the ED consultation. Thus, the intervention is the same for all patients, but the received advice is tailored to their prior responses when using the symptom checker.

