## Data collection and management

### Plans for assessment and collection of outcomes {18a}

All clinical study data will be registered in a REDCap database (electronic data collection form for clinical studies running on internal servers at Charité – Universitätsmedizin Berlin). The study timeline can be found in Fig. 1. To ensure that ED flow is not compromised through the study, parts of the baseline survey have been flexibilized.Baseline data:Sociodemographical data (e.g., age, sex, level of education)eHealth Literacy (eHEALS) [19]Self-reported health (MEHM) [20]Health anxiety (Item 1 of the German version of the Whiteley-Index WI-d, modified to Likert-scale) [21]Technical affinity (ATI-S) [22]Self-efficacy (ASKU) [23]Anxiety (VAS-A) [15]Patient’s stand-alone triage appraisalSymptom assessment data will be collected through the Ada Health appAn automatically in-app generated report will be downloaded and savedQuestionnaires pre-symptom assessment, after the symptom assessment (Ada), and after the physician encounter will be directly entered into the RedCap database by the participants. To reduce loss-to-follow-up, the survey after the physician encounter can be filled out up to 72h after the contact (e.g. on the ward or via telephone) if extraordinary circumstances prohibit the patient from taking the survey at the intended timepoint. Questionnaires used in the study are:PSQ [12]ZUF-8 [13]VAS-A [15]Trust scale of the CPQ [16]System Usability Scale (SUS) (only for the intervention group) [17]mHealth App Usability Questionnaire (MAUQ) (only for the intervention group) [18]Treating physicians fill out a paper-based survey after the first-patient encounter including the following items:Physician version of the PSQ [12]Triage appraisalRoutine clinical follow-up data after the patient-physician encounter will be collected by a study nurse and directly entered into the RedCap database.ICD-10 codesAssigned triage level (Manchester Triage System, MTS)Discharge typeLength of hospital stayDuration of waiting time

Patients not willing to participate in the trial will be offered to complete an anonymized version of the baseline survey in a paper-based form.

Data collection forms will be made available upon reasonable request by third, academic partners.

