## Discussion

The AKUSYM study is the first multi-center, randomized controlled trial to test the effect of a SAA on patient and physician-reported outcomes in acute care. We decided to provide the treating physicians with the recommendations of the app upfront to mimic integration into ED workflow. Results cannot be generalized to the setting where laypersons would use SAA at home for triage decisions or directed search for potential diagnoses of the symptoms they experience. Instead, study results could inform decision-makers on the implementation of a SAA into acute care to improve patient-physician interaction. We therefore experiment with a potential field of application for such apps.

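### Comparing the app with physicians who saw its result measures agreement, not accuracy, and a triage panel limited to discrepant cases leaves shared errors unreviewed

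*Protocol article*

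**What the plan says.** All places are in the protocol article.

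- **Diagnosis (Outcomes {12}, Other outcomes).** The text reads: "Diagnostic accuracy is measured by comparing the recommendations of the SAA with diagnoses given in the ED, after discharge and by an independent, external" expert panel that is blinded to the app. Nothing in this sentence limits the panel to a subset of cases.
- **Triage (same section).** The text reads: "Triage accuracy is measured by comparing the recommendation of the SAA with the MTS, triage appraisal of the treating physician in the ED", and then adds an "expert panel blinded to the recommendation given by the app for cases where discrepancies occurred". The restriction to discrepant cases appears only here. The section does not say which ratings must differ, or whether the comparators are combined into one figure.
- **What the physician has seen (Intervention description {11a}).** "The assessment and recommendations are printed by the study personnel and will be provided to the treating physician before the ED consultation". The Discussion confirms that this is deliberate: "We decided to provide the treating physicians with the recommendations of the app upfront to mimic integration into ED workflow".
- **When the physician's triage appraisal is recorded (Plans for assessment and collection of outcomes {18a}).** "Treating physicians fill out a paper-based survey after the first-patient encounter"; the triage appraisal is one of its items.
- **When the Manchester triage (MTS) level is set.** The Abstract places app use after initial triage, and the inclusion criteria require an MTS category at randomization.
- **Status.** Diagnostic and triage accuracy is objective 8, under Other objectives.

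**The concern.** There are two separate problems.

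First, app results exist only in the intervention group, and there the treating physician receives them before making the diagnosis and the triage appraisal. When those judgements later serve as references for the app, the reference is not independent of the test. A physician who adopts the app's answer makes the app look right. The plan blinds the panel to the app, which recognises this risk, but it keeps the exposed physician as a comparator under the name of accuracy.

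Second, a panel that sees only discrepant triage cases cannot find an error on which the app and its comparators agree. The two problems compound, because each wrong app answer that a physician adopts moves from the discordant group, which the panel sees, to the concordant group, which it does not. Urgency underestimated by both the app and the physician is the shared error that matters most for safety.

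**Working it through.** **The plan's own figures.** The article gives no figure for accuracy. Its sample size matters here only for the number of app users. A two-sample *t*-test at a standardized difference of 0.3, two-sided 5% level and 80% power needs 176 per group, so 352 in total, and 352 / 0.8 = 440. Both figures reproduce. App accuracy can therefore be measured in at most 220 patients, or 220 × 0.8 = 176 after the expected dropout.

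**Assumed inputs (none are in the document).** App accuracy a = 0.60. Unaided physician accuracy p = 0.80. Three urgency levels, as in the three eligible MTS categories. Errors are independent and fall equally on the two wrong levels. The physician adopts the app's answer with probability c = 0, 0.2 or 0.4. MTS accuracy m = 0.60 to 0.80. The panel is always right.

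**Step 1. Raw agreement with the physician, no panel.**
Agreement = c + (1 − c)[a·p + (1 − a)(1 − p)/2] = c + (1 − c)(0.48 + 0.04) = c + 0.52(1 − c).

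**Step 2. Panel triggered by app-physician disagreement only, concordant cases counted as correct.** A case is wrongly credited when the app is wrong and the physician gives the same wrong level.
Excess = (1 − a)[c + (1 − c)(1 − p)/2] = 0.4(0.1 + 0.9c) = 0.04 + 0.36c.

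**Step 3. Panel triggered if the app differs from the physician or the MTS.** The MTS must now share the same wrong level as well.
Excess = (0.04 + 0.36c)(1 − m)/2.

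**Step 4. Panel used only to settle MTS-physician disagreement.** The agreed level is the reference when the two concur. A correct app then loses credit when both concur on a wrong level.
Net = [(0.04 + 0.36c) − a(1 − p)(1 − c)](1 − m)/2 = (−0.08 + 0.48c)(1 − m)/2.

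| Reported app accuracy (true 60%) | c = 0 | c = 0.2 | c = 0.4 |
|---|---|---|---|
| Step 1, raw agreement | 52.0% | 61.6% | 71.2% |
| Step 2, app-physician trigger | 64.0% | 71.2% | 78.4% |
| Step 3, MTS also triggers (m = 0.80 to 0.60) | 60.4 to 60.8% | 61.1 to 62.2% | 61.8 to 63.7% |
| Step 4, tie-break of the reference | 58.4 to 59.2% | 60.2 to 60.3% | 61.1 to 62.2% |

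The excess is thus 4.0 to 18.4 points in Step 2 and 0.4 to 3.7 points in Step 3. In Step 4 the error runs from −1.6 to +2.2 points.

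**Sensitivity of Step 2.** With a perfect panel, a of 0.50 or 0.70, p of 0.80 or 0.90 and c from 0 to 0.3, the excess runs from 0.3 × 0.05 = 1.5 points (a = 0.70, p = 0.90, c = 0) to 0.5 × (0.3 + 0.7 × 0.1) = 18.5 points (a = 0.50, p = 0.80, c = 0.3).

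**Scale.** The 95% half-width for a proportion of 0.60 is 1.96 × √(0.24/220) = 6.5 points, or 7.2 points with 176 patients. Under Step 2 the bias at c = 0.2 (11.2 points) is larger than the sampling error. Under Step 3 it stays below it.

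**The case against.** A reader might infer that all reported app accuracy is biased upward. The document does not support that, for four reasons.

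- **Diagnosis has a sound comparator.** An external panel blinded to the app is named, without restriction to discordant cases. This stands. The ED diagnosis is still listed beside it under the same label.
- **The MTS is uncontaminated.** It is assigned before the app is used. This stands, and Step 3 shows how far it protects the triage result if disagreement with the MTS also sends a case to the panel.
- **The direction is not fixed for every comparison.** Raw agreement with an imperfect, uninfluenced physician understates accuracy (52% against 60%), and adoption of the app's answer only later reverses this. Under the tie-break reading the error can also go either way. Both stand. Upward bias is certain only where app-comparator agreement is counted as correct without review.
- **Pooling is not stated, and this is a condensed article.** Comparators reported separately would give several estimates, and the fuller documents may define what counts as a discrepancy. This stands as a limit on the size. It does not remove the point: the article already fixes the exposed physician as a comparator and the panel's restricted scope, and no later analysis plan can supply ratings that were never collected.

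Showing physicians the printout is a deliberate and explained choice for the randomised comparison, and this point does not question it.

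**Conclusion.** The point holds in limited form. The comparisons of the app with the ED diagnosis and with the treating physician's triage appraisal are open to incorporation bias and should be read as agreement. For triage, errors shared by the app and its comparators escape the blinded panel. If concordant cases are counted as correct, accuracy is overstated relative to a full panel rating.

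Under the stated assumptions the overstatement is about 4 to 18 points if app-physician disagreement alone triggers the panel, and about 0.4 to 4 points if app-MTS disagreement does too. The article does not say which applies, and it gives no data on app, physician or MTS accuracy or on how often physicians follow the app. Errors that are positively correlated rather than independent would raise these figures. The diagnosis panel and the MTS comparison are not affected, and neither are the primary and secondary outcomes. The change is worth making because it decides what can be concluded on objective 8, but it has no bearing on the trial's main result.

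**What to change.** Amend the two accuracy items under Outcomes {12}, Other outcomes:

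1. Name the blinded panel as the reference standard for both diagnosis and triage.
2. Have the panel rate triage in all intervention cases. Alternatively, have it rate all discordant cases plus a random sample of concordant ones, with each sampled concordant case weighted by the inverse of its sampling fraction. Define what counts as discordant.
3. State that the app printout is kept out of the panel's case file.
4. Report app versus ED diagnosis, and app versus treating-physician triage, as agreement. Keep the MTS as an independent comparator.

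The relabelling is free. The cost is some additional ratings by a panel that is already planned, in at most 220 patients. With the raw agreement of Step 1, rating every concordant case adds about 0.52 × 176 = 92 to 0.712 × 220 = 157 triage ratings, and sampling half of them halves that. The resulting accuracy figure may be less favourable to the app.
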